## Abstract

**Background:**

Sexual violence (SV) is a significant, global public health problem, particularly among young adults. Promising interventions exist, including prosocial bystander intervention programs that train bystanders to intervene in situations at-risk for SV. However, these programs suffer from critical weaknesses: (1) they do not address the proximal effect of alcohol use on bystander decision-making and (2) they rely on self-report measures to evaluate outcomes. To overcome these limitations, we integrate new content specific to *alcohol use within the context of prosocial bystander intervention* into an existing, evidence-based program, *RealConsent1.0*. The resulting program, *RealConsent2.0*, aims to facilitate bystander behavior among sober *and* intoxicated bystanders and uses a virtual reality (VR) environment to assess bystander behavior in the context of acute alcohol use.

**Methods:**

This protocol paper presents the design of a randomized controlled trial (RCT) in which we evaluate *RealConsent2.0* for efficacy in increasing alcohol- and non-alcohol-involved bystander behavior compared to *RealConsent1.0* or to an attention-control program (“*Taking Charge*”). The RCT is being implemented in Atlanta, GA, and Lincoln, NE. Participants will be 605, healthy men aged 21–25 years recruited through social media, community-based flyers, and university email lists. Eligible participants who provide informed consent and complete the baseline survey, which includes self-reported bystander behavior, are then randomized to one of six conditions: *RealConsent2.*0/alcohol, *RealConsent2.0*/placebo, *RealConsent1.0*/alcohol, *RealConsent1.0*/placebo, *Taking Charge*/alcohol, or *Taking Charge*/placebo. After completing their assigned program, participants complete a laboratory session in which they consume an alcohol (target BrAC: .08%) or placebo beverage and then engage in the Bystanders in Sexual Assault Virtual Environments (BSAVE), a virtual house party comprising situations in which participants have opportunities to intervene. Self-reported bystander behavior across alcohol and non-alcohol contexts is also assessed at 6- and 12-months post-intervention. Secondary outcomes include attitudes toward, outcome expectancies for, and self-efficacy for bystander behavior via self-report.

**Discussion:**

*RealConsent2.0* is the first web-based intervention for young men that encourages and teaches skills to engage in prosocial bystander behavior to prevent SV while intoxicated. This is also the first study to assess the proximal effect of alcohol on bystander behavior via a VR environment.

**Trial registration:**

Clinicaltrials.gov, NCT04912492. Registered on 05 February 2021

## Administrative information

Note: the numbers in curly brackets in this protocol refer to SPIRIT checklist item numbers. The order of the items has been modified to group similar items (see http://www.equator-network.org/reporting-guidelines/spirit-2013-statement-defining-standard-protocol-items-for-clinical-trials/).

## Introduction

### Background and rationale {6a}

Sexual violence (SV) is a major problem in the USA and globally [1–5] and exists on a continuum from “minor” behaviors (e.g., catcalling, verbal suggestions of intent of forced sex) to extreme behaviors such as attempted or completed rape [6]. One in four women and one in 26 men have experienced completed rape in the USA [7]. Both male and female young adults aged 18–24 experience the highest SV victimization across any age group [1, 5, 8–10]. Moreover, more than 80% of female and male victims of SV report experiencing victimization before age 25. However, despite decades of research, rates of SV victimization have not decreased [3, 11]. The consistently high incidence of SV is likely due to a major gap in the availability of effective SV prevention programming. To close this gap, critical weaknesses in the extant literature upon which these programs are based must be addressed. One key weakness, and the focus of the present project, involves the way in which SV prevention programming addresses alcohol use.

It is well-established that alcohol is a key contributor to SV, as research indicates that about 50–77% of SV incidents involve alcohol use by the victim, perpetrator, or both [12, 13]. Further, SV often occurs at or after attending bars or parties where attendees drink alcohol [14–16], and approximately 50–80% of men endorse perpetrating unwanted physical contact (e.g., pressing up against a woman from behind, grabbing a woman’s butt) in a bar or party setting [17]. Importantly, in addition to perpetrators and victims of SV, third-party “bystanders” are oftentimes consuming alcohol in situations in which SV is most likely to occur [18]. The bystander decision-making model, which encourages individuals to step in and intervene to prevent SV, is used extensively and effectively in SV prevention [2, 6, 19–25]. However, these prevention programs do not explicitly focus on alcohol use as a potential barrier to successful bystander invention. This is problematic because theory and research indicate that alcohol intoxication functions as a barrier to intervention across all steps of the decision-making process, thereby reducing the likelihood of bystander intervention [26–29]. Recent findings indicate that alcohol use is cross-sectionally associated with lower rates of bystander intervention, especially among men [18, 28, 30]. Although there have been studies that have examined the proximal effect of alcohol consumption on bystander intervention behaviors [30–39], only two of these [30, 37] have *used controlled alcohol administration methods* and assessed *observable bystander behavior* (e.g., verbalizations or actions to prevent SV).

Various SV programs have used the bystander model to increase bystander intervention [40]. One of these programs is *RealConsent1.0*, a web-based SV prevention and bystander intervention program that has been rigorously tested and found to be effective in preventing SV perpetration and increasing prosocial bystander behaviors among college men [23]. *RealConsent1.0 and other e*xisting programs address the role of alcohol in SV [23, 41, 42]; however, our review of the literature indicates that these programs do not integrate alcohol-specific content with the aim of (1) educating bystanders about how alcohol use functions as a barrier to intervention and (2) teaching strategies to compensate for these effects. We present a protocol for a definitive, multi-site RCT to address these limitations. The protocol has been extensively peer-reviewed as part of the funding application process.

## Objectives {7}

The overarching goal of this project is to evaluate the efficacy of *RealConsent2.0*, which includes new program segments for promoting prosocial bystander behavior among intoxicated men. This aim is grounded in the evidence-based premise [28, 43, 44] that integrating alcohol-specific content within the context of *RealConsent1.0* (i.e., “*RealConsent2.0*”) will enhance prosocial bystander behavior among intoxicated bystanders. As such, we sought to achieve this goal by testing two related research questions: (1) Does *RealConsent2.0* facilitate more prosocial bystander intervention (assessed within a virtual environment) among intoxicated men relative to two comparison conditions (i.e., *RealConsent1.0* and *Taking Charge*)? and (2) Does *RealConsent2.0* facilitate more prosocial bystander intervention (assessed at 6- and 12-month follow-up) involving alcohol-related events relative to the two comparison conditions?

## Trial design {8}

This trial is a 2 × 3 factorial, double-blind (i.e., participants and statistician), multisite, superiority randomized controlled trial with six parallel groups (see Fig. 1). The two independent variables are the web-based health promotion intervention (*RealConsent1.0*, *RealConsent2.0*, or *Taking Charge*) and beverage condition (Alcohol or Placebo). Eligible participants (40% of whom will be heavy-episodic drinkers) who provide informed consent will be randomized to one of six conditions using stratified, block randomization with equal allocation across groups. The primary study outcome is bystander decision-making and will be assessed via observable behaviors within a VR environment and via self-report within an online survey administered at baseline and 6- and 12-month post-intervention. This trial will include detailed, written instructions to achieve uniformity of the performance procedures, including screening, retention efforts, and adherence to CONSORT guidelines.

**Fig. 1 Fig1:**
[figure not shown]
CONSORT 2010 Flow Diagram

## Methods: Participants, interventions and outcomes

### Study setting {9}

The study is being implemented at two large, public universities in the USA: Georgia State University (Atlanta, GA) and University of Nebraska–Lincoln (Lincoln, NE). Recruiting from these two distinct geographical regions that vary in ethnic and racial diversity should maximize generalization of findings.

### Eligibility criteria {10}

#### Participant inclusion criteria

Age: 21–25 years, inclusiveGender: identifies as a man or transgender manAlcohol: must have consumed weight-based amount of alcohol (e.g., five drinks for weight of 160–189 lbs.) at least three times in the last yearLanguage: able to read and write English fluently

#### Participant exclusion criteria

Weight: over 250 lbs.Relationship status: in a relationship over 6 months; married/living togetherMedications/conditions: a condition or medication use in which alcohol consumption is medically contraindicatedNeurological disorders: diagnosis of a neurological disorderPsychiatric disorders: past or current diagnosis of bipolar disorder (I or II), schizophrenia, schizoaffective disorder, or any other psychotic disorderTreatment for alcohol or drug use: currently being treated for alcohol or drug problems; currently interested in seeking treatment for drinking or drug usePhysical disability: any physical disability that would prevent an individual from participating in the virtual reality task (self-reported and determined)Significant hearing problems: significant hearing problems that would prevent an individual from hearing and responding to the virtual reality task (self-reported and determined)Cardiac pacemakerAsthma: emergency room visit related to asthma in the past year; use of inhaler more frequently when drinking; use of oral steroid treatments for asthma in the past yearLegal: any legal restrictions against drinking (e.g., as a condition of probation or parole)Alcohol abstinence: individuals who consume alcohol monthly or less; individuals who have consumed the amount of alcohol they would be expected to drink during the lab session (determined by their weight) less than three times in the last yearHead injury: any past serious head injuries (as indicated by HELPS Brain Injury Screening Tool) [45]Acute psychiatric symptomatology: elevated psychological distress as indicated by a score greater than 65 on the Brief Symptom Inventory (BSI) [46]

### Who will take informed consent? {26a}

Trained research staff will obtain informed consent via Zoom during the baseline session. Research staff take each potential participant through the informed consent process and provide opportunities for questions. Participants who agree to participate are asked to sign the informed consent form electronically.

### Additional consent provisions for collection and use of participant data and biological specimens {26b}

N/A

We do not have additional consent provisions for collection and use of participant data. We are not collecting biological specimens as part of this trial.

## Interventions

### Explanation for the choice of comparators {6b}

The Pragmatic Model for Comparator Selection in Health-Related Behavior Trials was used to select an optimal comparator intervention [47]. The main objectives of this trial are to determine whether (1) *RealConsent2.0* is efficacious in increasing alcohol-involved and non-alcohol involved bystander behavior and (2) observed effects in *RealConsent2.0* are greater than the original *RealConsent1.0*. The first objective requires a comparator, such as the use of an attention control that can isolate certain intervention components or underlying mechanisms of behavior change [47]. Accordingly, an Internet-based program called *Taking Charge* was selected as the comparator intervention to serve as the attention control*. Taking Charge* was chosen as the attention-matched control, as it mimics *RealConsent2.0* in several ways, but does not overlap in content. *Taking Charge* is of similar length and access is through a browser-based site but optimized for the smartphone environment. It is interactive, dynamic, and engaging, and it includes multi-media components such as video and graphic presentations imbedded within the context of general health promotion. *Taking Charge* encompasses five modules; however, one module, “Alcohol and Health” was not used in this trial as the content overlaps with *RealConsent*2.0 and could potentially affect study outcomes. The following *Taking Charge* modules were used: (1) My Health Profile—individual assessment of health behaviors with personalized feedback; (2) Staying Healthy—includes information on healthy eating, physical activity, and self-care; (3) Managing Stress—information on identifying stressors and cognitive-behavioral techniques for reducing stress, and (4) Resources/Tools for Goal Setting and Tracking Progress.

### Intervention description {11a}

The original *RealConsent1.0* is a web-based educational program that has two primary goals: (1) to prevent SV perpetration and (2) to increase bystander intervention for SV. These goals are achieved by affecting theoretically and empirically derived mediators, such as increasing knowledge of and skills for safely intervening, correcting misperceptions in normative beliefs, affecting negative attitudes toward date rape, increasing knowledge of effective consent, affecting masculine gender roles, enhancing communication skills, and increasing empathy for victims [23, 48, 49]. *RealConsent1.0* is delivered via a password-protected Web portal that allows participants to access the program either via the web or their mobile phones. The program consists of six 30-min modules with each ranging in number of segments (1–14) and types of activities. Each module involves interactivity, didactic activities, and entertainment-education [50, 51] in the form of 12 mini-episodes of a serial drama called “Crew,” which allows for modeling of positive behaviors and illustration of both positive and negative outcome expectations for perpetrating SV and for bystander intervention.

*RealConsent2.0* incorporates newly developed content into the different modules of *RealConsent1.0* with the objective of increasing knowledge of how alcohol impairs cognitive processing, in particular attentional processes (see Alcohol Myopia Theory [52]), and thus affects their ability: (1) to notice a SV event, (2) to identify events as high risk for SV, (3) to take responsibility to intervene, and (4) to formulate a plan (see integrative framework for the proximal effect of alcohol on bystander intervention for SV [28]. *RealConsent2.0* also attempts to focus men’s attention on salient peer and social norms (see Integrated Model of sexual assault and acquaintance rape [41]) and encourages them to apply good decision-making strategies that can be used while drinking alcohol, enables them to identify alcohol-related risky situations for a sexual assault, helps build new skills to enhance prosocial intervening while drinking alcohol, and develops a positive self-evaluation attached to SV intervention while consuming alcohol or within alcohol contexts.

Following the completion of the baseline survey, participants are randomized to either *Taking Charge, RealConsent1.0*, or to *RealConsent2.0* and are subsequently provided access to their respective programs via email. Each intervention is self-paced, and participants are encouraged to complete their respective programs within 2 weeks.

#### Alcohol administration

At baseline, participants are randomly assigned to either consume an alcohol beverage (told alcohol, receive alcohol) or a placebo beverage (told alcohol, receive no alcohol) in a subsequent laboratory session. Alcohol participants are administered two drinks consisting of an overall dose of 0.80 g/kg body weight of 95% ethanol USP mixed in a 1:5 ratio with orange juice. The beverage is poured into two glasses in equal quantities. This single alcohol dose reliably produces BrACs between .08% and .12% within 20–40 min of beverage consumption. Placebo participants are administered an isovolemic beverage consisting of 5 parts orange juice and 1 part tonic water divided equally into two glasses. Each glass of the placebo beverage is mixed with 4 c.c.s. of 95% ethanol USP and surface layered with an additional 4 c.c.s. of 95% ethanol USP. The rims of the glasses are also sprayed with alcohol.

Regardless of beverage condition, all participants are told that they are receiving a “moderate” dose of alcohol. Twenty minutes are allotted for beverage consumption. Drinks are administered at equally spaced times during the 20-min interval to control for drinking rate. BrACs for participants are monitored every 5 min after finishing their beverages with the Alco-Sensor FST breath analyzer (Intoximeters, Inc., St. Louis, MO). Alcohol participants begin the B-SAVE task after reaching .08% on the ascending limb of the BrAC curve. Placebo participants begin the B-SAVE task immediately after they finish their drinks because placebo manipulations are most effective shortly after beverage consumption [53, 54].

To verify the success of the placebo manipulation, the Subjective Intoxication Scale [55] is administered before and after beverage consumption. Participants are asked to rate their current level of intoxication on a scale from 0 (not at all drunk) to 11 (more drunk than I have ever been). An estimate of how many standard drinks participants believe they consumed is also assessed. A successful placebo manipulation is evidenced by participants’ reporting they ingested “some” alcohol and felt “somewhat” intoxicated [56]. Any participant who denies consuming alcohol or provides a subjective intoxication rating of “0” is excluded from analysis.

#### Criteria for discontinuing or modifying allocated interventions {11b}

By participant request only.

#### Strategies to improve adherence to interventions {11c}

Participants are encouraged to complete their assigned intervention within 2 weeks. Study staff send a total of three reminder emails (one email every 4 days during the 2-week period). In addition, we provide a $10 incentive to complete an acceptability survey following completion of each intervention module.

#### Relevant concomitant care permitted or prohibited during the trial {11d}

Participating in an alcohol or drug treatment program is an exclusion criterion, but we do not monitor or prohibit participation during the trial.

#### Provisions for post-trial care {30}

It is the policy of each affiliated institution to not pay for post-trial care; however, mental health and counseling services are available.

#### Outcomes {12}

The SPIRIT diagram is displayed in Fig 2. The primary outcome measures are bystander behavior using the B-SAVE [57] 1-month post-intervention and self-reported bystander behavior during the past 6 months measured using the 44-item Bystander Behavior Scale (BBS) [58] at baseline and 6- and 12-month post-intervention.

**Fig. 2 Fig2:**
[figure not shown]
SPIRIT diagram of trial schedule of enrolment, intervention, and assessments. Note: BSAVE (Bystanders in Sexual Assault Virtual Environments), BBS (Bystander Behavior Scale), BSABI (Barriers to Sexual Assault Bystander Intervention); OEIS (Outcome Expectancies for Intervening Scale); BES (Bystander Efficacy Scale); BAS (Bystander Attitudes Scale); SES-SF (Sexual Experience Survey Short Form); ROLBS (Reactions to Offensive Language & Behavior Scale); SEI (Self-Efficacy to Intervene Scale); DDQ (Daily Drinking Questionnaire); AESASVQ (Alcohol Expectancies Regarding Sex, Aggression, and Sexual Vulnerability Questionnaire); CTS (Revised Conflict Tactics Scale); RES (Rape Empathy Scale); DRS (Differential Reinforcement Scale)

Within each of the five at-risk scenarios depicted in the BSAVE, participants are prompted at two points (with a flashing microphone icon) to verbalize their response in that situation—thus providing ten opportunities to intervene in sexual risk situations. A team of research assistants will use audio recordings of participants’ open-ended responses to the risk scenes, as well as non-verbal behaviors captured by the VR system, to code intervention behaviors in response to each risk scenario. The most central code of interest will reflect the presence or absence of intervention attempts (0 = no, 1 = yes) in response to each of the two SV intervention opportunities within each of five risk scenes. An index measure will be created based on these responses that can range from 0 to 10 and will be used in data analyses.

For each item on the BBS, participants are asked to report their engagement with a specific bystander behavior (i.e., engaged in behavior, did not engage in behavior, no opportunity to engage in behavior). Following completion of the 44 items, follow-up questions are administered to assess additional information relevant to each bystander behavior in which the participant reportedly engaged or did not engage. For behaviors in which the participant reportedly engaged, the follow-up questions assess the number of times participants engaged in the behavior on a 1 (1 time) to 3 (3 or more times) scale. Questions also prompt participants to recall the most recent time they engaged in the behavior and report whether (1) they were drinking alcohol, (2) others were drinking alcohol, and (3) the people involved were friends or strangers. For behaviors in which the participant reportedly did not engage, follow-up questions assess the number of times they had the opportunity to intervene but did not do so using a 1 (1 time) to 3 (3 or more times) scale. Questions also prompt participants to recall the most recent time they did not engage in the behavior (but had an opportunity to do so) and report whether (1) they were drinking alcohol, (2) others were drinking alcohol, and (3) the people involved were friends or strangers.

#### Secondary outcomes

The following secondary measures will be assessed.Barriers to sexual assault bystander intervention as measured using the 16-item *Barriers to Sexual Assault Bystander Intervention Scale* [59]. Each item is rated on a 1 (strongly disagree) to 7 (strongly agree) scale, with higher mean scores indicating more barriers to intervention.Outcome expectancies for intervening as measured using the 17-item *Outcome Expectancies for Intervening Scale* [60]. Each item is rated on a 1 (strongly disagree) to 7 (strongly agree) scale, with higher mean scores indicating greater positive expectancies for intervening.Bystander efficacy as measured using the 14-item *Bystander Efficacy Scale* [60]. Response options for each item range from 0 to 100% confidence. A score is created by subtracting the mean of these 14 items from 100 to create a scale of perceived efficacy, with higher scores reflecting greater bystander efficacy.Bystander attitudes as measured using the 12-item *Bystander Attitudes Scale* [61]. Each item is rated on a 1 (minimum) to 5 (maximum) scale, with higher mean scores indicating higher intentions of intervening.Sexual violence perpetration as measured using the 35-item *Sexual Experience Survey Short Form Perpetration* [62]. Participants indicate the number of times that they perpetrated SV using verbal coercion, incapacitation, threats of physical force, and physical force on a scale ranging from 0 (never) to 3 (3 or more times). The mutually exclusive scoring system will be used [63]. The goal is to count people only once according to the most severe act perpetrated.

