
#### Participant timeline {13}

##### Sample size {14}

Sample size requirements were determined via a Monte Carlo simulation study based on Aim 2 analysis strategy, which will require a larger sample than Aim 1 analyses. The primary outcome for Aim 2 will be intervention proportion: the number of times each participant engaged in prosocial bystander behavior divided by the number of sexist or violent situations they encountered during a given assessment period. Sample size is therefore based on the number per treatment group needed to detect clinically meaningful effects on intervention proportion. Calculations were based on 80% power, level of significance of .05, and two-tailed statistical tests. Clinically meaningful treatment efficacy was based on previous research [23, 71] and was defined as having between a small and medium effect size between group intervention proportions (Cohen’s *h* ≥ .30). In this RCT, this effect size translated into a 15% point difference between groups, at a minimum, and could potentially translate to a clinically significant increase in bystander intervention for those who receive *RealConsent2.0*. Assuming control participants intervene in approximately 50% of all sexist or violent *non-alcohol* situations they encounter, those who receive RealConsent1.0 will intervene in 65% of those non-alcohol-related situations; those who receive RealConsent2.0 will also intervene in 65% of non-alcohol-related situations. For *alcohol-related* situations, we expect those in control and in RealConsent1.0 to intervene approximately 30% of the time whereas for RealConsent2.0, we expect 45% of the time they will intervene. Based on these proportion differences, a total of 484 participants are needed ~161 in each intervention group). We expect between 20% attrition based on previous work. To achieve adequate power, we estimated a needed sample size of at least 605 to maintain complete data for 484 participants for the per protocol analysis. Additionally, this sample size allows us to detect small differences (7%) in intervention rates within the VR paradigm as a function of intervention and beverage conditions, as well as their interactions.

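### The Bystander Efficacy score is defined as 100 minus mean confidence but read as higher = greater efficacy, so following the text reverses the sign of this secondary outcome

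*Protocol article*

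**What the plan says.** The Bystander Efficacy Scale is one of five measures in the Secondary outcomes section of the protocol article, introduced by "The following secondary measures will be assessed". The article makes three statements about it:

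- **Item scale:** "Response options for each item range from 0 to 100% confidence".
- **Formula and direction, both in one sentence:** the score is formed by "subtracting the mean of these 14 items from 100 to create a scale of perceived efficacy, with higher scores reflecting greater bystander efficacy".

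The article mentions no reverse-keying or recoding of the items, and gives no other scoring rule for this scale. The Abstract also lists self-efficacy for bystander behavior among the secondary outcomes.

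**The concern.** An item answered in percent confidence gives a larger number to a more confident man. Subtracting the mean from 100 turns that round, so the score measures lack of confidence. The same sentence then reads it as efficacy.

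If the scale is scored and interpreted by this sentence, a programme that strengthens men's confidence to intervene appears to weaken it, and a programme that weakens it appears to help. Three features of the trial make the error hard to notice:

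- **Mixed directions.** Higher is favourable for outcome expectancies and attitudes but unfavourable for barriers, so one scale moving against the others would not look odd in itself.
- **Blinding.** Under Who will be blinded {17a}, the biostatistician does not know the conditions, so an implausible direction by arm would not show while scores are being built.
- **Data sharing.** Under {31c} the data are to be released publicly, so outside users who follow the published rule could repeat the reversal.

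**Working it through.** **Inputs, all from Secondary outcomes in the protocol article**

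- Number of items: 14 ("Bystander efficacy as measured using the 14-item" Bystander Efficacy Scale).
- Item range: 0 to 100, in percent confidence.
- Scoring rule: S = 100 − M, where M is the mean of the 14 items.
- Stated direction: higher S means greater efficacy.

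The article gives no numerical result for this scale, so there is no figure to reproduce. The check is whether the formula yields the stated direction.

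**Step 1: evaluate the formula over its range**

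| Mean confidence M | Score as written, 100 − M | Plain mean |
|---|---|---|
| 0 | 100 | 0 |
| 25 | 75 | 25 |
| 50 | 50 | 50 |
| 60 | 40 | 60 |
| 70 | 30 | 70 |
| 80 | 20 | 80 |
| 100 | 0 | 100 |

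The slope of S on M is −1 throughout. The man with no confidence gets the highest possible score and the fully confident man the lowest. The stated direction is not reproduced.

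**Step 2: effect on a contrast between arms**

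For arm means M_T and M_C, the difference in scores is

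(100 − M_T) − (100 − M_C) = −(M_T − M_C).

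Take assumed means of 70 and 60, chosen only for illustration. The true difference is 70 − 60 = +10. The score gives 30 − 40 = −10.

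A simulation with 161 men per group, and item values drawn around assumed means of 60 and 70 and truncated to 0–100, gave +9.9 on raw confidence and −9.9 on the score. The correlation between the two was −1.

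**Step 3: what changes and what does not**

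Because Var(100 − M) = Var(M), the standard error of a mean difference is the same under either scoring. In a linear model with an identity link, the absolute estimate and the two-sided p-value are also the same. Only the sign and its reading change. A significant benefit would become an equally significant apparent harm.

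**Step 4: reach**

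Under Sample size {14}, "Sample size is therefore based on the number per treatment group needed to detect clinically meaningful effects on intervention proportion". The 484 completers, and the 605 to be enrolled (484 / 0.80 = 605), do not depend on this scale. Nor do the two primary measures under Outcomes {12}, the virtual-reality behavior index and the Bystander Behavior Scale.

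**Step 5: can another part of the article reconcile the statements?**

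They would agree only if a higher item value meant less confidence. The stated response scale says the opposite. The subtraction is not a general convention of the article either: barriers, outcome expectancies, attitudes, rape empathy and peer disapproval are all scored as plain means with a stated direction.

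**The case against.** The best counter-argument is that the text shows an inconsistent sentence, not a wrong result. A reversed sign needs three things together: items stored as confidence, the subtraction actually coded, and the output read as higher = better. The article cites the source instrument and does not reproduce its item wording, anchors or any recoding. If responses were keyed so that higher means less confidence, the subtraction would be correct and switching to the plain mean would introduce the very error it is meant to remove. The scale is also one of five secondary measures. The transformation is linear, and the score can be rebuilt from the item responses before reporting. Finally, the note to Fig. 2 lists a separate Self-Efficacy to Intervene Scale, so not all efficacy measurement is affected.

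Much of this stands as a limit. The consequence is conditional, it concerns the Bystander Efficacy Scale only, and item keying should be confirmed before any code is changed. It does not remove the contradiction. Reverse-keying has no support in the text and conflicts with a response scale expressed as confidence. Nor is this a detail left to a fuller document: the article states both a formula and a direction, and they disagree.

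**Conclusion.** The concern holds. With items scored as confidence, the formula and the stated direction are incompatible, and nothing else in the article reconciles them. Applied as written, the sign of every effect on this secondary outcome is reversed at unchanged size: a 10-point gain becomes a 10-point loss.

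The contradiction rests only on the plain reading that a higher percentage means more confidence. It needs no assumption about effect size, variance or sample size. The wrong sign in the results rests on the further condition that the analysts compute and interpret the score as the sentence directs. The primary outcomes, the sample size and the other secondary measures are not touched. It should be corrected before analysis, because the error would be invisible in the test statistics and the correction is nearly free.

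**What to change.** 1. Confirm from the survey as fielded that a higher item value records more confidence, as the article states.
2. State one rule with a matching direction:
   - **Preferred:** the score is the plain mean of the 14 items, from 0 to 100, with higher values meaning greater efficacy. This matches the stated direction and the scoring of the neighbouring mean-based scales.
   - **Alternative:** keep 100 minus the mean, rename the score perceived inefficacy, and state that lower is better.
   - If step 1 shows that the items are keyed the other way, keep the subtraction and the stated direction, and correct the description of the response scale.
3. Check that the scoring code follows the chosen rule, for example by confirming that a record with every item at 100% confidence receives the score the rule implies (100 under the plain mean, 0 under the inefficacy score).
4. Carry the same rule into the documentation for the public data release.

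The cost is one sentence and one line of scoring code, with no new data and no loss of power.
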